### Follow-Up Period

Follow-up assessments with questionnaires will be conducted. During the 24-week unsupervised follow-up period, no participants will undergo special therapy, with the exception of routine cervical care.

It is important to acknowledge that every subsequent patient will schedule an appointment in advance via telephone and visit the outpatient department. Subsequently, the outcome assessors will aid patients in completing the questionnaire, will conduct and document physical examinations, and will administer cervical CT scans.

The outcome assessors will establish an electronic information group, inviting all participants to join. Throughout the follow-up period, any adverse events or physical discomfort experienced in any circumstance will be promptly reported within the information group.

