**Methods:**

This study is a prospective randomized controlled clinical trial that will be conducted at a single center and that has a follow-up period of 24 weeks. A total of 96 patients diagnosed with AJS will be recruited from outpatient and inpatient clinics at Shanghai Baoshan Hospital of Integrated Traditional Chinese and Western Medicine. These patients will be randomly assigned to either the experimental group (SCRM) or the comparison group (basic cervical manipulation [BCM]). Treatment sessions consisting of SCRM or BCM will be administered twice a week for a duration of 4 weeks. Clinical monitoring indicators include the presence or absence of clinical symptoms as recorded on a symptom recording form, cervical imaging examination findings using cervical computed tomography, degree of neck pain measured by a visual analog scale (VAS), cervical range of motion assessed through cervical mobility measurement, degree of vertigo evaluated using the Vertigo Symptoms Scale-Chinese Version (VSS-C), and adverse events that may occur during the follow-up period. The time points for data collection and follow-up are baseline and postintervention (weeks 4, 8, 12, 16, 20, and 24).

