### Blinding

Participants will be unaware of their group assignment and will remain unaware of receiving SCRM or BCM treatment. The outcome assessors will also be unaware of the randomization allocation and will not be involved in the intervention process. The manual therapists will not be able to be blinded owing to their involvement in performing the interventional protocols. However, they will not participate in the outcome measurements or statistical analyses and will be instructed to refrain from disclosing treatment details to the outcome assessors or participants. The statistician will remain blinded to the group allocation until the completion of the statistical analyses.

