### SCRM Technique

The primary technological approach in SCRM involves applying pressure with the thumb on the spinous process, transverse process, or pedicle of the patient’s axis while simultaneously rotating the cervical spine in an effort to restore it to its original alignment. AJS is categorized into 8 distinct techniques, which are determined by the specific imaging characteristics of the atlantoaxial joint. Figure 2 shows the comprehensive classification of AJS according to X-ray findings. Each technique within these categories employs different SCRM methods. When there is a simple asymmetrical gap between the lateral mass of the atlantoaxial joint and the odontoid process, the spinous process of the axis remains aligned with the midline of the spinous process, yet the discrepancy in distance between the lateral mass of the left and right atlas and the dentate process is evident. If the left block displays a 2-mm greater distance compared with the right block, it falls under type A (left oblique type). Conversely, if the right block displays a 2-mm greater distance compared with the left block, it is classified as type B (right oblique type). When there is a simple misalignment of the axis spinous process relative to the midline of the spinous process, the distance between the lateral masses of the left and right atlas and the dentate process is either equal or exhibits a difference within a 2-mm range. However, the spinous process of the axis deviates from the midline of the spinal axis. If the spinous process of the axis is located at the left of the midline, it is classified as type C (left rotation type). Conversely, if the spinous process of the axis is located at the right of the midline, it is categorized as type D (right rotation type). The types can mix as follows: when type A merges with type C, it is referred to as type AC; when type A merges with type D, it is referred to as type AD; when type B merges with type C, it is referred to as type BC; and when type B merges with type D, it is referred to as type BD. The SOPs of SCRM according to the different types are presented below [18].

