### BCM Technique

The BCM technique does not differ depending on the type of AJS. The SOP of BCM for patients with AJS (all types) is as follows [18]. First, the patient assumes a seated position, and the manipulation therapist stands behind the patient’s left side. Second, the therapist manipulates the patient’s jaw by flexing their left elbow and applies pressure to the occipital area with their right hand, which is supporting the occipital bone with the right palm and supporting the other 4 fingers. Third, the therapist gradually rotates the patient’s head to the left until reaching the active limit position and then instructs the patient to relax their neck while continuing to rotate the head to the passive limit position using both hands. During this process, a momentary force is exerted to further facilitate the left rotation of the patient’s head, resulting in audible clicking sounds emanating from the neck. Fourth, the therapist performs the 3 steps on the right side of the patient. It is important to note that the therapist can freely select one side (left or right) of the patient for the procedure.

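### Adverse events are reported in one shared group, run by the blinded assessors and open to both arms, which puts blinding at avoidable risk

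*Protocol article*

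**What the plan says.** Under Follow-Up Period, the protocol article states: "The outcome assessors will establish an electronic information group, inviting all participants to join". It adds that, during follow-up, "any adverse events or physical discomfort experienced in any circumstance will be promptly reported within the information group". The same section has these assessors help patients fill in the questionnaire and carry out the physical examinations.

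Under Blinding, the article says of participants: "Participants will be unaware of their group assignment and will remain unaware of receiving SCRM or BCM treatment". Of the assessors it says: "The outcome assessors will also be unaware of the randomization allocation and will not be involved in the intervention process". The only non-disclosure instruction is addressed to the manual therapists, who "will be instructed to refrain from disclosing treatment details to the outcome assessors or participants". Nothing comparable is stated for participants.

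Under Primary Outcome, efficacy is built from a 0-10 symptom rating (NRS). The efficacy rate is calculated at visit 1 (week 4) and again at visit 6 (week 24), and the recurrence rate at visit 6. The VAS and the VSS-C are also completed by the patient.

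**The concern.** The reporting channel brings together the people whom the Blinding section means to keep apart from knowledge of treatment: patients of both arms and the assessors who examine them. A patient who reports a sore neck in the group may well mention what the therapist did. Other patients can compare that with their own experience, and an assessor who knows the two techniques can infer the arm.

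Therapists cannot be blinded in this trial, so protection of the self-rated outcomes rests on the patients and the assessors. If patients learn that their treatment differs from that of others, their ratings may shift. If an assessor learns the arm, both the help given with questionnaires and the measurement of cervical mobility may shift. Either could bias the comparison of SCRM with BCM, in a direction that the document does not allow one to predict.

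**Working it through.** No arithmetic reproduces or refutes this point, because the article gives no figure for it. The check sets the sections side by side.

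1. **Who is in the group.** Follow-Up Period: set up by the outcome assessors, with all participants invited. There is one group, and no separation by arm is described.

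2. **Who must stay blind.** Blinding: participants and outcome assessors. Both are in the group.

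3. **Can a report reveal the arm?** SCRM Technique describes "applying pressure with the thumb on the spinous process, transverse process, or pedicle of the patient’s axis while simultaneously rotating the cervical spine", with the hand position varied by AJS type. BCM Technique says "the therapist manipulates the patient’s jaw by flexing their left elbow and applies pressure to the occipital area with their right hand", the same for all types. Shared features are the seated position, the relaxation step of about 10 minutes, a rotational thrust and usually a click. A patient alone has nothing to compare with. Two patients who exchange accounts do. For an assessor, one description that mentions a thumb on the neck bone, or an elbow under the jaw, could be enough. This assumes that the assessor knows the two procedures, which is likely at a centre that uses both but is not stated.

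4. **What restrains disclosure.** Blinding: an instruction to therapists only. Neither Blinding nor Follow-Up Period mentions private messages, moderation or an instruction to participants.

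5. **Which outcomes are open to influence.** The symptom NRS, VAS and VSS-C are patient ratings. Cervical mobility is measured by the outcome assessor. The CT distances are measured by two radiologists, three times each, and are less exposed through this route.

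6. **When the exposure falls.** Follow-Up Period speaks of a 24-week follow-up without special therapy, while Table 1 puts the end of treatment at week 4 and the last visit at week 24. Two readings are possible:

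| Reading | Group runs | Outcomes exposed |
|---|---|---|
| Opens after treatment | weeks 4 to 24 (24 − 4 = 20 weeks) | week-24 efficacy and recurrence rates; week-4 efficacy rate largely spared |
| 24 weeks counted from baseline | weeks 0 to 24, including treatment | week-4 efficacy rate as well |

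The week-24 rates are exposed under both readings.

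7. **Size.** The document gives no rate of group use, no content of messages and no assessment of blinding success. No bias can be computed from it.

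**The case against.** The strongest reply is that the group is for adverse events and discomfort, not for discussing technique, and that the two arms share much of what a patient feels. Patients who found that their manoeuvres differ would still not know which one is experimental. The consent text is not available, so patients may already have been told that two techniques are compared. This stands to the extent that unblinding is a possibility and not a certainty. It does not remove the risk: an assessor need not be told which arm is experimental if the technique itself is recognisable, and nothing stated keeps participants from describing it.

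A reader might go further and infer three things that the document does not support.

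- **That adverse events at the manipulation sessions go unrecorded.** There are 2 × 4 = 8 sessions. Table 1 has six adverse-event checks (weeks 4, 8, 12, 16, 20 and 24), none before the end of treatment, and the abstract speaks of "adverse events that may occur during the follow-up period". But Table 1 has no treatment-session column for any measure, and the Adverse Events section commits to recording any event and tracking it promptly. Session forms are commonly left to the full protocol, which is not shown. A count of unrecorded sessions, or a claim that early reactions depend on weeks of recall, would be an inference from silence.
- **That shared reporting invalidates the chi-square safety comparison.** Nothing in the article shows that one patient's report depends on another's.
- **That the primary result as a whole is compromised.** If the group opens after treatment, the week-4 efficacy rate is largely protected.

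**Conclusion.** The point holds as a conflict between two sections: a shared group run by the assessors sits badly with the blinding of participants and assessors, and the only stated safeguard binds neither. It is a design weakness that should be corrected. It does not show that blinding has failed or will fail.

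The size is unknown. The exposed results are the week-24 efficacy and recurrence rates and the self-rated secondary outcomes during follow-up. The week-4 efficacy rate joins them only if the group runs during treatment. The conclusion rests on three assumptions: that both arms share one group, as the text reads; that participants can see one another's messages, as the word group implies; and that some reports would describe the manoeuvre.

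**What to change.** Replace the shared group with private one-to-one reporting, by phone or direct message, to named study personnel who do not assess outcomes. Keep these messages from the assessors. Ask participants not to describe their technique to assessors or to other participants, and add this to the Blinding section beside the instruction to therapists. State when the reporting channel opens, so that the 24-week follow-up and Table 1 agree. It is also worth confirming that events at treatment sessions are recorded under the general commitment in the Adverse Events section.

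Costs and limits:

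- Messages must be handled one by one.
- The recipient must be chosen with care. The Discussion assigns research assistants to screening, selection and follow-up, so some of them may themselves be assessors.
- A change of study procedure needs board approval under Ethical Considerations.
- The gain is partial. By the end of May 2024, 76 patients had been included. Against the 96 given in the abstract, 96 − 76 = 20 were still to enter (93 − 76 = 17 against the 93 under Study Design). Only these and patients still in follow-up would benefit. For the others, the report should state that the shared group was used.

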### Outcome Measurement

The following baseline descriptive data will be obtained using questionnaires: age, gender, marital status, education level, occupation, basic medical history, and drug combination. A summary of all measures and follow-up time points in this trial is shown in Table 1.

#### Primary Outcome

##### Efficacy Rate

The clinical symptoms of all subjects will be recorded and evaluated using the numerical rating scale (NRS), which is composed of a horizontal line having a length from 0 to 10 cm, with “0” indicating “normal” and “10” indicating “unbearable.” We will refer to the efficacy evaluation standards in the “Diagnostic and Therapeutic Efficacy Standards for Traditional Chinese Medicine Diseases” issued by the China Administration of Traditional Chinese Medicine in 1994.

We define clinical cure as a decrease of more than 80% in the NRS score for clinical symptoms and the ability to live and work normally. We define clinical improvement as a decrease of 20% to 80% in the NRS score for clinical symptoms. We define clinical cureless as a decrease of less than 20% in the NRS score for clinical symptoms. We define clinical recurrence as the reappearance of the original symptoms after treatment, with the degree being equivalent to or greater than that before treatment.

All patients will be followed up, and the efficacy rate will be calculated at visit 1 after the intervention. The efficacy rate and clinical recurrence rate will be calculated at visit 6. The calculation formulas are as follows:

Efficacy rate = ([number of clinical cure cases + number of clinical improvement cases – number of clinical cureless cases] / total number of patients) 100

Clinical recurrence rate = (number of clinical cureless cases / [number of clinical cure cases + number of clinical improvement cases]) 100

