### Withdrawal Criteria

The withdrawal criteria are as follows: (1) severe or intolerable adverse reactions during the observation process; (2) persistent or progressive symptoms and no suitability for participation in the trial; (3) risk of health damage (such as sudden serious complications); and (4) voluntary withdrawal or interview miss for other reasons.

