### Sample Size

The sample size calculation is based on our previous clinical research in patients with cervical spondylosis of the nerve root type, using the same primary outcome instrument. The efficiency of SCRM is 89.5%, while that of BCM is 54.6%. The sample size calculation formula is as follows:

The α is .05 and 1–β is .90. According to estimations, 48 participants per group are needed considering that this is a long-term follow-up that is expected to have a dropout rate of no greater than 20%.

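### The primary efficacy-rate formula subtracts the non-responders, so the reported rate is not a proportion and is not a rate that the planned chi-square test can compare.

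*Protocol article*

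**What the plan says.** All references are to the protocol article.

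- **Efficacy Rate (primary outcome).** Each patient is graded by the change in a 0–10 symptom score. Cure is "a decrease of more than 80% in the NRS score for clinical symptoms and the ability to live and work normally". For the middle grade: "We define clinical improvement as a decrease of 20% to 80% in the NRS score for clinical symptoms". For failure: "We define clinical cureless as a decrease of less than 20% in the NRS score for clinical symptoms". The efficacy rate is then cure cases plus the "number of clinical improvement cases – number of clinical cureless cases] / total number of patients", times 100. It is calculated at visit 1 and again at visit 6.
- **Sample Size.** "The efficiency of SCRM is 89.5%, while that of BCM is 54.6"%, taken from the group's earlier study in nerve-root-type cervical spondylosis "using the same primary outcome instrument". The section sets α = 0.05, power 0.90, dropout of no more than 20%, and 48 participants per group. It does not say by which formula the two rates were obtained.
- **Statistical Analysis.** Rates are to be compared between groups with a Pearson chi-square test, for superiority, at a one-sided 0.05 level.

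No other section corrects or explains the subtraction.

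**The concern.** A responder rate already penalises a failure once: the patient is in the denominator but not in the numerator. Subtracting the failures as well penalises them a second time and turns the endpoint into a net score. A net score can be negative and is not a number of patients out of a total. The chi-square test and the sample-size section both deal in ordinary proportions, so the primary endpoint as printed does not fit the test planned for it.

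At stake is the headline result. A team that follows the formula will report primary rates that readers take for response percentages but that are not, with a group difference up to about twice the real one. The analyst is also left without a clear statement of what goes into the test.

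**Working it through.** **Inputs.** Planning rates 89.5% and 54.6%, α = 0.05, power 0.90, 48 per group and 20% dropout (Sample Size); one-sided level 0.05 and Pearson chi-square (Statistical Analysis); the three categories and the formula (Efficacy Rate). Evaluable patients after 20% dropout: 48 × 0.8 = 38.4, taken as 38.

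**1. The plan's own figure.** Treating 89.5% and 54.6% as ordinary proportions, the pooled two-proportion formula, two-sided with continuity correction, gives 39 evaluable per group. Then 39 / 0.8 = 48.75, so 49, or 39 × 1.2 = 46.8, so 47. The stated 48 lies between them. A one-sided calculation gives 27 (34 after dropout), or 32 (40 after dropout) with the correction, and does not reach 48. That discrepancy is a separate matter.

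**2. What the printed formula computes.** Let p be the share cured or improved. If everyone is classified, the cureless share is 1 − p, and

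rate = p − (1 − p) = 2p − 1.

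| True responder rate | Printed formula |
|---|---|
| 89.5% | 2(0.895) − 1 = 79.0% |
| 54.6% | 2(0.546) − 1 = 9.2% |
| Difference 34.9 points | Difference 69.8 points |

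The rate is negative whenever fewer than half the patients respond. At p = 0.546 the binomial probability of that is 21.6% with 48 patients and 23.1% with 38.

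**3. The gap in the categories.** A fall above 80% without normal living and working is not cure, and improvement stops at 80%. If a share g of patients is unclassified but stays in the denominator, the cureless share is 1 − p − g and the rate becomes 2p − 1 + g. The doubling is then no longer exact, but the result is still a net score.

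**4. Conditional: net counts entered in the chi-square test.** With q = 2p − 1, the test would assume a per-patient variance of q(1 − q), while the true variance of the net score is 4p(1 − p).

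- p = 0.72: 4(0.72)(0.28) = 0.806 against 0.44 × 0.56 = 0.246, a ratio of 3.3.
- p = 0.895: 4(0.895)(0.105) = 0.376 against 0.79 × 0.21 = 0.166, a ratio of 2.3.

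Exact enumeration with no true difference, 48 per arm, one-sided 5%, negative counts set to 0:

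| p in both arms | Net counts | Responder counts |
|---|---|---|
| 0.72 | 18.7% | 5.0% |
| 0.895 | 14.0% | 5.1% |

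**5. Conditional: planning rates that are themselves net values.** Inverting, p = (1 + rate)/2 gives (1 + 0.895)/2 = 94.75% and (1 + 0.546)/2 = 77.3%, a difference of 17.45 points. Exact one-sided chi-square power at 38 evaluable per arm is then 74.1% (71% by the normal approximation), against the stated 90%. If the planning rates are plain proportions, dropping the subtraction leaves the sample size unchanged.

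**The case against.** The strongest reply is that a statistician would cross-tabulate responder status by group, whatever the printed percentage says. That test is valid, with rejection close to 5% under no difference. This stands. A reader might infer that the plan's false-positive rate is several times 5%, but the Statistical Analysis section nowhere says that net counts will be the cell counts. The 14% to 19% describes a literal misuse, not a stated procedure.

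A reader might also infer that the formula contradicts the rates behind the sample size, or that the trial is underpowered. The Sample Size section does not say how 89.5% and 54.6% were calculated. The Introduction gives earlier efficacy rates of 94.74% and 89.47%. These fit 18/19 and 17/19 as plain proportions; with 19 fully classified patients a net value of 18/19 is impossible, although with 38 patients both readings fit. The documents therefore do not favour net planning rates, and the lower power remains only a possibility to be excluded.

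Finally, a reader might link this to the withdrawal criterion of "persistent or progressive symptoms and no suitability for participation in the trial" and infer that failures will vanish from the analysis. The formula divides by the total number of patients, and no section removes withdrawn patients from it. Handling of missing outcomes is commonly left to the analysis plan, which is not shown.

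None of this rescues the formula. The subtracted term is spelled out in words, so it is not a symbol lost in text extraction.

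**Conclusion.** The primary efficacy rate is wrong as written. Applied literally, it reports 2p − 1 in place of p and doubles the group difference: 69.8 points instead of 34.9 at the planning rates. The doubling is exact only if every patient falls into one of the three categories. The categories do not ensure that, and the documents give no figure for how often the gap would occur.

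Two consequences are conditional. The type I error of about 14% to 19% needs net counts to be used as cell counts. The one-sided power of about 74% needs the planning rates to be net values and 38 evaluable patients per arm. The documents state neither condition. What is certain is a misreported primary rate and an undefined input to the primary test.

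**What to change.** 1. In Efficacy Rate, define: efficacy rate = (clinical cure + clinical improvement) / total number of patients × 100, with no subtraction.
2. In Statistical Analysis, say that the chi-square test is run on responder versus non-responder counts by group.
3. Count a fall above 80% without normal living and working as improvement, so that the categories cover every assessed patient.
4. In Sample Size, state that 89.5% and 54.6% are plain responder proportions. If they are net values, restate the power.

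The cost is a formula and a few sentences, through whatever amendment approval the Ethical Considerations section requires. No new data are needed. Reported rates change scale and the group difference will look smaller. If the planning rates prove to be net values, the cost is higher: 90% power would need 66 evaluable per arm one-sided (66 / 0.8 = 82.5, so 83 with dropout), against 48 planned. The change should be settled before unblinding.

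### The clinical recurrence rate counts all cureless patients over responders, so it contradicts the protocol's own definition of recurrence and gives the odds of non-response at visit 6

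*Protocol article*

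**What the plan says.** Under Primary Outcome, Efficacy Rate, the protocol article sets up four categories.

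- Cure, where living and working must also be normal: "We define clinical cure as a decrease of more than 80% in the NRS score for clinical symptoms and the ability to live and work".
- Improvement: "We define clinical improvement as a decrease of 20% to 80% in the NRS score for clinical symptoms".
- Cureless: "We define clinical cureless as a decrease of less than 20% in the NRS score for clinical symptoms".
- Recurrence: "We define clinical recurrence as the reappearance of the original symptoms after treatment, with the degree being equivalent to or greater than that before treatment".

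On timing it states: "The efficacy rate and clinical recurrence rate will be calculated at visit 6". The efficacy rate is also calculated at visit 1. Two formulas follow. The efficacy rate is (cure + improvement − cureless) / total × 100. The other is "Clinical recurrence rate = (number of clinical cureless cases / [number of clinical cure cases + number of clinical improvement cases", again multiplied by 100.

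The recurrence category appears in neither formula. Nothing limits the cureless cases to patients who had responded earlier, and no other section gives a different recurrence formula.

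**The concern.** A recurrence rate should say how many patients who got better then got worse again. This formula takes its numerator from a different category, one that requires no earlier response. A patient who never benefited is therefore reported as a recurrence.

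The index stands under the primary outcome heading and is the only one in the trial labelled as recurrence. As printed, a difference between the arms in plain non-response at week 24 would be published as a difference in relapse, even if nobody relapsed.

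**Working it through.** The protocol states no expected recurrence rate, so there is no figure to reproduce. The check compares the definition with the formula and then evaluates the formula.

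**Step 1. Definition against formula.** They differ in two ways.

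- *Earlier response.* Recurrence needs symptoms that reappear. Cureless needs only a fall below 20%, so never-responders enter the numerator.
- *Severity.* Recurrence needs symptoms at or above the pretreatment degree, that is, no decrease. A patient going from NRS 5 to 4.5 has a 10% decrease. That patient is cureless but does not meet the recurrence definition.

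**Step 2. What the formula computes.** Assume that every patient falls into cure, improvement or cureless, and let r be the share with cure or improvement at visit 6. Then:

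- recurrence formula: R = 100 × (1 − r) / r, the odds of non-response;
- efficacy formula, as a fraction: E = r − (1 − r) = 2r − 1;
- hence R = 100 × (1 − E) / (1 + E).

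R is fixed once the visit 6 efficacy rate is known. It passes 100% when r < 0.5 and is undefined at r = 0.

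**Step 3. Size when nobody relapses.** Inputs from Sample Size: 48 per group, planning rates 89.5% (SCRM) and 54.6% (BCM). Suppose each patient has the same status at visits 1 and 6. True recurrence is then 0% in both arms. The protocol does not say whether the planning rates are plain responder shares or net rates under its own efficacy formula, so both are shown.

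| Reading of planning rates | Arm | Responder share r | Printed formula |
|---|---|---|---|
| Plain share | SCRM | 43/48 | 5/43 = 11.6% |
| Plain share | BCM | 26/48 | 22/26 = 84.6% |
| Net rate | SCRM | (1 + 0.895)/2 = 0.9475 | 0.0525/0.9475 = 5.5% |
| Net rate | BCM | (1 + 0.546)/2 = 0.773 | 0.227/0.773 = 29.4% |

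With unrounded shares the plain reading gives 10.5/89.5 = 11.7% and 45.4/54.6 = 83.2%.

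**Step 4. The formula cannot separate relapse from non-response.** Take 26 responders and 22 cureless patients at visit 6. If those 22 never responded, true recurrence is 0/26 = 0%. If all 48 responded at visit 1 and 22 returned to at least the pretreatment level, true recurrence is 22/48 = 45.8%. The formula gives 84.6% both times.

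**Step 5. Chance of a value above 100% in BCM.** This needs more cureless patients than responders. With r = 0.546 the binomial probability is about 0.22 for 48 patients and about 0.23 for 38 (48 × 0.8 = 38.4, after 20% dropout). With r = 0.773 it is below 0.001 for either number.

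**The case against.** Several things can fairly be said for the plan.

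*Durability is still measured.* A reader might infer that the trial cannot say whether benefit lasts. The documents do not support that. The efficacy rate is also calculated at visit 6. Table 1 schedules symptoms, VAS and cervical mobility at every visit to week 24, VSS-C at weeks 4, 16 and 24, and imaging at weeks 4 and 24. This stands in full.

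*Relapsed patients are not left out.* Someone back at or above pretreatment severity at visit 6 has no NRS decrease and is therefore cureless. The fault is that others are added to them, not that they are missing.

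*The formula does not simply reward early response.* It depends on status at visit 6, so an arm with a strong initial response and many later relapses would show a high value. It favours the arm with fewer non-responders at visit 6, for whatever reason.

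*The larger illustration rests on one reading.* The efficacy formula subtracts cureless cases, and the planning data are said to use the same instrument for the primary outcome. The net reading is therefore open, and it shrinks the figures. The planning rates also come from patients with nerve root type cervical spondylosis, not AJS.

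*The formula may mean visit 6 cureless cases over visit 1 responders.* The text does not say so. Without limiting the numerator to visit 1 responders, never-responders would still be counted. In the no-change example the results would be identical. Even with that limit, the severity mismatch would remain.

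None of these points removes the contradiction between definition and formula. It may well be a drafting slip, but it is what the protocol prints.

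**Conclusion.** The point holds for this one index. The printed recurrence rate contradicts the definition given in the same section, is not a proportion, and repeats the visit 6 efficacy rate on another scale.

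With true recurrence at 0% in both arms it would report about 11.6% against 84.6%, or about 5.5% against 29.4%, depending on how the planning rates are read. Those figures assume 48 patients per arm for the plain reading, every patient in one of the three classes, and no change between visits 1 and 6. The contradiction itself needs none of these assumptions. Values above 100% are a realistic prospect only for BCM, and only on the plain reading.

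This should be fixed but does not threaten the trial's main conclusion. The recurrence rate sits beside the efficacy rate, the sample size does not depend on it, and the Statistical Analysis section does not name it.

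**What to change.** Replace the formula under Efficacy Rate with:

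> Clinical recurrence rate = (number of patients with cure or improvement at visit 1 who meet the stated definition of recurrence at visit 6) / (number of patients with cure or improvement at visit 1) × 100.

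The numerator then lies within the denominator, so the result stays between 0 and 100%. In the no-change example it gives 0/43 and 0/26, as it should.

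Add one sentence saying that the rate is descriptive, because its denominator is selected by response after randomisation and the two arms' responders need not be comparable. The between-group comparison of lasting benefit stays with visit 6 response in all randomised patients.

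The cost is one formula and one sentence, through the protocol's amendment route. No new data are needed, because Table 1 already schedules symptoms at every visit and the efficacy evaluation at visits 1 and 6.
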